### Provisions for post-trial care {30}

The University Hospital of Martinique (UHM), this trial’s sponsor, has contracted an insurance cover upon the Lloyd’s Insurance Company (ID: MCIEEA21042) for its public liability as well as that of any person involved in the trial, which is in accordance with the French public health code.

### Outcomes {12}

Our primary outcome will consist in the decrease of the self-reported cocaine craving as assessed with the French Craving Experience Questionnaire (CEQ; [53, 54]. The CEQ is an 11-item retrospective measure of cocaine craving containing two subscales: craving strength (CEQ-S) and frequency (CEQ-F). Each item is completed by the participants on a 10-point scale, from “not at all” (1) to “extremely” (10). The CEQ has shown good psychometric properties [54]. Means of CEQ-S and CEQ-F total scores will be analyzed. Finally, the CEQ will be administered before treatment (V0), after 2 weeks of treatment (V1; VRCET vs. PCET), post-treatment (V2; VRCET + vs. PCET), and 1-month post-treatment (V3; VRCET + vs. CET). The CEQ-S will be administrated immediately after a 7-min VRE to a cocaine-related situation, with a similar scenario to the CET situation 5 (Table 1) but across different virtual environments, avatars, and item appearances (Fig. 9). The CEQ-F will be administrated retrospectively, targeting the last 14-day period. (Table 4)

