**Methods:**

Fifty-four inpatients hospitalized for CUD will be randomized in one of two intensive 3-week treatment arms: 10 meetings/2-week treatment of VRCET plus 5 meetings/1-week treatment of memory-focused cognitive therapy (MFCT; experimental arm), or 15 meetings/3-week treatment of PCET (active control arm). The Craving Experience Questionnaire (CEQ – F & S) will be used to assess the primary outcome, i.e., the post-treatment decrease of self-reported cocaine craving frequency (within the past 2 weeks) and intensity scores (in VR exposure to cocaine cues). Secondary endpoints include urinary, physiological, and self-reported cocaine use-related measures. Assessments are scheduled at pretreatment, after 2 weeks of treatment (i.e., VRCET vs. PCET), post-treatment (3 weeks, i.e., VRCET + MFCT vs. PCET), and at 1-month follow-up. Acceptability will be evaluated via (i) the Spatial Presence for Immersive Environments – Cybersickness along VRCET and (ii) the Client Satisfaction Questionnaires after 2 weeks of treatment and post-treatment.

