**Discussion:**

This study will be the first to evaluate the acceptability and efficacy of VRCET for CUD, as a psychotherapeutic add-on, to reduce both cocaine craving frequency and intensity. Additionally, this study will provide evidence about the specific interest of VRCET, compared to a non-VR-based CET, as a cue reactivity and exposure paradigm for treating substance use disorders.

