### Sample size {14}

We calculated a required sample size of 54 participants to randomize with G*Power [64], on the basis of two-tailed independent *t*-tests, to detect large effect from our experimental treatment (VRCET +) over our control therapeutic condition (PCET) in reducing cocaine craving [39, 65], given a 0.05 statistical significance threshold, a 0.95 statistical power, and accounting for potential dropouts in our hospitalized inpatients.

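### Two primary craving scores (CEQ-F and CEQ-S) share one 0.05 threshold, with no rule on whether one or both must be significant

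*Protocol article*

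**What the plan says.** The abstract of the protocol article defines the primary outcome as "the post-treatment decrease of self-reported cocaine craving frequency (within the past 2 weeks) and intensity scores (in VR exposure to cocaine cues"). The Outcomes {12} section confirms that there are two scores: "Means of CEQ-S and CEQ-F total scores will be analyzed". They are collected differently. CEQ-F is a recall over the previous 14 days. CEQ-S is completed straight after a 7-minute virtual-reality exposure to cocaine cues.

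Statistical methods {20a} plans independent t-tests on the T0-to-T2 change, VRCET+ against PCET. Bonferroni correction appears there only for the Wilcoxon signed-rank and Sign tests, which replace the t-tests if distributional assumptions fail. It is not tied to the pair of primary scores.

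Sample size {14} arrives at 54 participants from a calculation for two-sided t-tests between the arms. Its stated purpose is "to detect large effect from our experimental treatment (VRCET +) over our control therapeutic condition (PCET) in reducing cocaine craving". The other settings of that calculation are listed as follows: "given a 0.05 statistical significance threshold, a 0.95 statistical power, and accounting for potential dropouts in our hospitalized inpatients". The size of the large effect and the dropout rate are not given as numbers.

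The only wording that bears on a joint requirement is in the abstract's discussion, where the treatment is meant "to reduce both cocaine craving frequency and intensity".

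**The concern.** Which score or scores decide success is part of defining the primary outcome. The article does not rank the two scores, combine them, divide alpha between them, or say that both must be significant. Two readings remain open. Under one, the stated 0.05 is exceeded. Under the other, the stated power of 0.95 is not reached.

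The gap could matter in practice because the scores may diverge. CEQ-S is measured inside virtual reality, the medium in which the experimental arm has 40 therapy exposures, while the control arm is treated with laptop slides. CEQ-F is a recall that does not depend on the exposure medium. The trial is open-label and its outcomes are mostly self-reported, so blinding does not protect against settling the rule after results are seen.

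As written, whether any correction applies also depends on the shape of the observed data: none is stated for the t-tests, while Bonferroni is stated for the fallback.

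**Working it through.** **Inputs from the protocol article.** Two primary scores (Outcomes {12}); two-sided independent t-tests, alpha 0.05, power 0.95, total 54 (Sample size {14}); 1:1 allocation (Trial design {8}), hence 27 per arm.

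**Assumptions, because the article gives no figure.** Standardised effect d = 1.0 or 0.8; correlation r between the two test statistics from 0 to 0.9; jointly normal test statistics; both scores tested at 0.05. The last is inferred from the single threshold and the plural t-tests; it is not stated per score.

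**Step 1: reproduce the 54.** For a two-sample t-test with n per arm, the noncentrality is d × √(n/2) on 2n − 2 degrees of freedom.
- d = 1.0, n = 27: 1.0 × √13.5 = 3.674, 52 df, power 0.950. This gives 54 exactly, with nothing left for dropout.
- d = 0.8, n = 27: 0.8 × 3.674 = 2.939, power 0.822. Power of 0.95 would need 42 per arm (84).

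The article's figure therefore matches one test on one score at 0.05 with d = 1.0, or a larger effect with some dropout. It holds no allowance for a second score.

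**Step 2: error rate if either score suffices.** Familywise error = 0.05 + 0.05 − P(both significant under the null). At r = 0 this is 1 − 0.95² = 0.0975.

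| r | P(both) | Familywise error |
|---|---|---|
| 0 | 0.0025 | 9.75% |
| 0.3 | 0.0049 | 9.5% |
| 0.5 | 0.0093 | 9.1% |
| 0.7 | 0.0165 | 8.3% |
| 0.9 | 0.0296 | 7.0% |

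For jointly normal statistics, r = 0 gives the maximum.

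**Step 3: power if both are required at 0.05.** The chance of success with neither score truly affected is P(both) above, and with only one affected it is at most 0.05, so alpha holds. Joint power is the bivariate normal probability that both tests succeed, each with the single-test power from step 1.

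| r | d = 1.0 (single test 0.95) | d = 0.8 (single test 0.82) |
|---|---|---|
| 0 | 0.902 | 0.676 |
| 0.3 | 0.907 | 0.699 |
| 0.5 | 0.912 | 0.718 |
| 0.7 | 0.920 | 0.742 |
| 0.9 | 0.932 | 0.776 |

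At d = 0.8 the total shortfall from 0.95 runs from 0.174 (0.950 − 0.776) to 0.274 (0.950 − 0.676). Of this, 0.128 (0.950 − 0.822) is already present with one score, which is 47% to 73% of the shortfall.

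**Step 4: power if alpha is split.** At 0.025 per score with 27 per arm, power per score is 0.91 at d = 1.0 and 0.73 at d = 0.8. Power of 0.95 at 0.025 and d = 1.0 needs 32 per arm (64) before dropout.

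**The case against.** The best case for the plan is that this is a condensed article and the statistical analysis plan is not shown. Multiplicity procedures are often left to that plan, and the abstract's mention of both frequency and intensity leans towards requiring both, in which case alpha is not inflated. That stands in part: the mechanics of Holm or of a testing sequence may well sit elsewhere. But whether the two scores are joint or alternative criteria belongs to the definition of the primary outcome. The abstract's phrase describes an aim and is not a decision rule. The article also does address correction, and places it only in the fallback.

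Three stronger readings are tempting, and the document does not support them.
- **A reader might infer that the trial's error rate is 9.8%.** That needs an either-score rule, which the article never states, and uncorrelated scores. Two subscales of one questionnaire are more likely to be positively correlated.
- **A reader might infer that requiring both scores leaves power far below 0.95.** The figures near 0.7 need d = 0.8, whereas the article says only that the effect is large. At d = 0.8 a single test already misses 0.95 by a wide margin, which is a separate sample-size matter. At d = 1.0 the joint requirement costs about 2 to 5 percentage points.
- **A reader might take the article's main Discussion as confirming that both scores must improve.** That sentence speaks of cocaine use, not craving, and adds the 1-month follow-up, so it settles nothing.

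**Conclusion.** The concern holds as a missing success rule for two primary scores. Its size depends on the rule eventually applied:
- **Either score suffices:** familywise error about 7% to 9.5% for correlations from 0.9 down to 0.3, with a ceiling of 9.75% at correlation 0, against the stated 5%.
- **Both required:** error at most 5%, but joint power about 0.90 to 0.93 at d = 1.0, or about 0.68 to 0.78 at d = 0.8, against the stated 0.95.

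These figures assume 27 analysed per arm, the same effect on both scores, and 0.05 for each test. Dropout would lower the power figures further. No choice of effect size or correlation removes the problem, because the article leaves the choice between the two rules open.

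**What to change.** By dated amendment, before outcome data are analysed, state one rule for CEQ-F and CEQ-S, and apply it whether the t-test or a rank test is used. Any of these would do:
- **Fixed sequence at 0.05.** For example, CEQ-F first, and CEQ-S only if CEQ-F is significant. The order is the sponsor's choice. The first test keeps its full alpha and no extra participants are needed; the second score can be claimed only after the first.
- **Holm across the two scores.** The first step is at 0.025, with power per score of 0.91 at d = 1.0 and 27 per arm. Restoring 0.95 there would take 64 participants before dropout.
- **Both significant at 0.05.** This fits the abstract's wording best and needs no alpha split. Joint power should be restated as about 0.90 to 0.93 at d = 1.0.

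Restate the power to match the chosen rule, with the assumed effect size and dropout rate as numbers. Recruitment was under way from May 2023, so the amendment should record when the rule was fixed in relation to any look at outcome data. If an unseen analysis plan already holds such a rule, citing it with its date would suffice.

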## Methods: participants, interventions, and outcomes

### Study setting {9}

The PICOC trial will be conducted in 2 French overseas national centers (Martinique University Hospital and Saint-Esprit Hospital, Martinique, France). Eligible patients will be recruited and hospitalized in the 2 addictology inpatient residential services, where data will be collected during the trial. The Martinique University Hospital (UMH) is the largest French and English-speaking Caribbean University Hospital. In addition, the UMH is a 1600-bed institution, including 680 medical, 273 surgical, obstetrics, and 30 intensive care unit beds. Both the UMH and Saint-Esprit Hospital are specialized in treating SUDs, offering out and residential hospitalization services.

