### Participants

#### Eligibility criteria {10}

##### Inclusion criteria

Patients must meet the following criteria to be eligible for the study:Patient with a CUD (SCID-5 CV; [41]) and treated as an inpatient at one of the two investigation centers (i.e., Martinique University Hospital or Saint-Esprit Hospital)URICA score indicating “Action” or “Maintenance” readiness to stop using cocaine [42]Patient affiliated to a social health insurance planPatient ≥ 18 years of age

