#### Experimental or active control therapy (3 weeks)

Participants included will start therapy (experimental or active control arm) within 1 week after the inclusion visit as follows:VRCET + (experimental arm): 2-week phase of 10 VRCET sessions, followed by a 1-week phase of 5 MFCT sessions. The VRCET phase will essentially consist of 40 VRE to a progressive hierarchy of 5 diversified cocaine-related situations. The MFCT phase will be in accordance to the “Memory Focused Cognitive Therapy for Cocaine Use Disorder” therapist guide (for request: [39]), and will consist of cognitive restructuring and memory reconsolidation procedures along with imagery exposure to arousing memories of cocaine use.PCET (active control arm): 3-week phase of 15 PCET sessions. The PCET phase will essentially consist of 60 VRE to a progressive hierarchy of 5 diversified cocaine-related situations.

Both VRCET + and PCET sessions will last 1 h 30 min and will be delivered in an intensive 1:1 intervention format, on a daily basis, from Monday to Friday. The facilitator of VRCET + and PCET may differ, but each patient will have only one facilitator.

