#### In and post-treatment measuring times (V1, V2, and V3)

The first measuring time (T1) will take place after 2 weeks of treatment, at the 11th treatment session and prior to start the MFCT (experimental arm) or second PCET (active control arm) phase. This will thus allow for comparing short-term research primary and secondary outcomes between VRCET and PCET, after 10 consecutive sessions of exposure.

The second measurement time (T2) will take place at the end of treatment (week 3), at the 15th and last treatment session. This will thus allow for comparing short-term research primary and secondary outcomes between VRCET + (10-session VRCET and 5-session MFCT) and PCET, after 15 consecutive sessions.

The third and last measuring time (T3) will consist in a follow-up visit taking place 1 month after the end of treatment (week 8). This will thus allow for comparing medium-term research primary and secondary outcomes between VRCET + (10-session VRCET and 5-session MFCT) and PCET, 1 month after 15 consecutive sessions of each therapeutic arm. Patients’ participation will end after this visit.

For each of these measurement times, subjective self-report questionnaires and objectives measures related to research objectives will be administered (Fig. 10).

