## Assignment of interventions: allocation

### Sequence generation {16a}

The Research Electronic Data Capture (REDCap) secure web application will be used for randomizing participant allocation to the experimental or active control therapeutic arm. The randomization will be stratified per investigation center (UHM or SEH), with an allocation ratio of 1:1 to the therapeutic arms and following a randomly permuted per-block order.

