### Plans to promote participant retention and complete follow-up {18b}

Prior to each measurement time (T0, T1, T2, and T3), participants will be reminded of the therapeutic and scientific importance of dully completing each intervention and assessment phase. For the follow-up assessment, the investigators will contact the participants to collect study outcomes. A 20 € voucher will be offered to any outpatient participant in the follow-up assessment phase willing to use public transport for coming to their respective investigation center. Participants will be reminded that they may discontinue their consent to participate at any time during protocol, without justifying any reason and with no impact on their TAU. Data collected in participants who withdraw their consent will be analyzed.

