## Statistical methods

### Statistical methods for primary and secondary outcomes {20a}

Statistical analyses for principal and secondary outcome will be computed from self-report scales raw total scores or physiological signals (i.e., blood pressure, skin temperature and conductance) using, respectively, R Statistical [66] and OpenSignals (© PLUX S.A.) software. Our comprehensive data working R code, including R packages and inferential statistical hypothesis testing assumptions (Gaussian distribution, homoscedasticity, etc.), will be made available. For each primary or secondary variable of interest, descriptive statistics (n, min, max, median, q1, q3, iqr, mean, sd, se, and mean ci) will be computed using the *rstatix R* package. Primary inferential statistical analyses will consist of two-tailored independent *t*-tests on score changes between T0 (baseline) and T2 (post-treatment) in the experimental (i.e., VRCET +), compared with the active control therapeutic arm (PCET). In case of mostly non-normal variable distributions but symmetrical score differences around the median, Friedman and Bonferroni-corrected Wilcoxon signed-rank tests will be performed to test and contrast score differences between the conditions using *stats* and *rstatix R* packages [67]. In case of non-symmetrical paired score differences, Bonferroni-corrected Sign tests will be performed. Causal mediation analyses will be adjusted for confounding factors. Cohen’s d, Kendall’s W, and Cliff’s delta effect sizes for score changes across treatment arms (“negligible,” “small,” “medium,” and “large” effect for Cliff’s d inferior to 0.15, 0.33, 0.47, and superior to 0.47; [68]) with 95% CIs will be computed using *irr* and *effsize R* packages.

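### CEQ-F only: the 14-day recall at T0 can mix days before and after admission while the T2 recall cannot, so the unadjusted T0–T2 change test may carry avoidable noise

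*Protocol article*

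**What the plan says.** The primary outcome is the decrease in self-reported craving on the CEQ. For its frequency subscale, Outcomes {12} states: "The CEQ-F will be administrated retrospectively, targeting the last 14-day period". The strength subscale (CEQ-S) is instead completed straight after a 7-minute virtual exposure and has no 14-day window.

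The inclusion criteria require a patient "treated as an inpatient at one of the two investigation centers". Neither the criteria nor the account of the inclusion visit gives a minimum or maximum stay before V0. On what follows V0, the article says "Participants included will start therapy (experimental or active control arm) within 1 week after the inclusion visit as follows". T2 "will take place at the end of treatment (week 3), at the 15th and last treatment session". On setting, Study setting {9} says: "Eligible patients will be recruited and hospitalized in the 2 addictology inpatient residential services, where data will be collected during the trial". Outpatient status appears only at follow-up: "A 20 € voucher will be offered to any outpatient participant in the follow-up assessment phase".

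Statistical methods {20a} plans independent t-tests on "score changes between T0 (baseline) and T2 (post-treatment" and names no covariate for them. If distributions are not normal, it turns to Friedman, Wilcoxon signed-rank or Sign tests. On allocation: "The randomization will be stratified per investigation center (UHM or SEH", so time since admission is not a stratum.

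**The concern.** The two recall windows that form the CEQ-F change score need not describe the same setting. A patient included on the day of admission recalls two weeks in the community at T0. A patient included two weeks or more into the stay recalls only the unit. At T2 both recall days after admission. If craving is more frequent outside the unit, the first patient shows a drop that the second does not, whatever the therapy does.

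Two things are at stake. The first is precision: variation between patients in the pre-admission share enters the error term of a t-test on raw change, in a trial of only 27 per arm. The second is interpretation: the outcome is worded as a decrease, and part of any decrease within an arm could reflect admission alone. The protocol's background describes craving as triggered by exposure to cocaine cues, so an effect of moving to a residential unit is plausible on its own reasoning, although its size is not given.

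**Working it through.** **Timing.** Let L be the days from admission to V0. The share of the T0 window before admission is f = max(0, 14 − L)/14, which is 1 at L = 0, 0.5 at L = 7 and 0 at L ≥ 14. Sessions run Monday to Friday for three weeks, so session 15 falls on about day 19 from the first session. The 14 days before it begin around the end of treatment week 1. The T2 window thus lies after V0 and after admission for every patient.

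**Room for L to vary.** Recruitment {15} gives 30 beds and up to 200 patients a year. At full occupancy that is 30 × 365 / 200 ≈ 55 bed-days per patient. V0 to T2 takes up to about 7 + 19 = 26 days. Occupancy is not stated, so this shows only that L could exceed 14 days.

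**The plan's own figure.** For a two-sided t-test at alpha 0.05 and power 0.95, 27 per arm (54 in total) is exactly what d = 1.0 requires, with no dropout. At d = 0.8, 54 patients give power 0.822. The article gives no numeric d, so both are used below.

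**Assumptions, none of them in the documents.**
- The CEQ-F SD is 1 apart from the admission effect.
- The T0–T2 correlation rho is 0.5 or 0.7.
- Craving frequency outside exceeds that inside by D = 0.5, 1 or 2 SD.
- f is spread evenly over 0 to 1, so Var(f) = 1/12.

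**Variance of the change score:** 2(1 − rho) + D²/12.
- rho = 0.5: 1 + 0.0208 = 1.021 (+2%) at D = 0.5; 1.083 (+8%) at D = 1; 1.333 (+33%) at D = 2.
- rho = 0.7: 0.6 + 0.0208 = 0.621 (+3%); 0.683 (+14%); 0.933 (+56%).

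**Residual variance under ANCOVA.** With T0 alone it is 1 − rho²/(1 + D²/12). With T0 and the in-unit share it is 1 − rho².
- rho = 0.5: 0.755, 0.769 and 0.813 at D = 0.5, 1 and 2, against 0.750 (excess 0.7%, 2.6%, 8.3%).
- rho = 0.7: 0.520, 0.548 and 0.633, against 0.510 (excess 2.0%, 7.4%, 24%).

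**Power at 27 per arm**, for an effect of d = 0.8 in units of the change-score SD without admission variation. The change-test column is the noncentral t. The ANCOVA columns are simulated (40,000 trials per row), so they include the degrees of freedom spent and chance covariate imbalance.

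| rho | D | Planned change test | ANCOVA, T0 only | ANCOVA, T0 + in-unit days |
|---|---|---|---|---|
| 0.5 | 0.5 | 0.815 | 0.91 | 0.91 |
| 0.5 | 1 | 0.791 | 0.90 | 0.90 |
| 0.5 | 2 | 0.705 | 0.89 | 0.90 |
| 0.7 | 0.5 | 0.809 | 0.87 | 0.87 |
| 0.7 | 1 | 0.771 | 0.85 | 0.86 |
| 0.7 | 2 | 0.638 | 0.80 | 0.87 |

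At d = 1.0, rho = 0.5 and D = 1, the planned test falls only from 0.950 to 0.934.

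**Sensitivity to the spread of f.** If every patient has the same f, there is no loss. If half have f = 0 and half f = 1, Var(f) = 0.25, and at D = 1 the variance rises by 25% (rho = 0.5) or 42% (rho = 0.7).

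**Within-arm change.** With mean f of 0.5, the average drop owed to admission is D/2, that is 0.25 to 1 SD, with the same expectation in both arms.

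**The case against.** Nothing in the article is misstated on this point. The 14-day window is used consistently. A rule on time since admission could sit in the full protocol, and covariates are often left to an analysis plan; neither document is shown. That carries weight, but the article does fix the primary test as an unadjusted comparison of change scores, and that choice can be assessed as written.

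The size rests wholly on assumption. The documents give no admission effect, no correlation and no distribution of time since admission. If patients enter at a similar point of their stay, or if D is 0.5 SD or less, the loss is trivial. The SD implicit in the planned standardised effect may also already include this variation, in which case the nominal power is not reduced, although adjustment would still gain precision. All of this stands.

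The remedy is also mostly ordinary baseline adjustment. The table confirms it: at D = 0.5 the in-unit-days term adds nothing.

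A reader might infer more than the documents support:
- *That the arm comparison is biased.* It is not. Randomisation gives the admission effect the same expectation in both arms, and chance imbalance is covered by the test's error rate.
- *That T2 recall consists only of in-unit days.* This is the expected case, given the setting and the mention of outpatients only at follow-up, but no sentence requires patients to stay until T2.
- *That the decrease certainly contains an admission effect.* No figure in the documents shows one.
- *That the whole primary outcome is affected.* CEQ-S is not.
- *That the plan will read within-arm decreases as efficacy.* The Objectives and the primary test both compare arms, and the Discussion itself warns against causal attribution without a comparator.

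**Conclusion.** The point holds for CEQ-F as a matter of precision and interpretation. The T0 window may mix settings in a proportion that differs between patients, the T2 window lies after admission, and the planned t-test on raw change has no term to absorb the difference. Under an even spread of recall days and an admission effect of 0.5 to 2 SD, the change-score variance rises by about 2% to 33% at correlation 0.5, or 3% to 56% at 0.7. The upper ends need a 2 SD effect, for which the documents offer no support.

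The between-arm contrast remains unbiased. A T0–T2 decrease within an arm cannot be attributed to therapy. The fallback tests deserve the same caution: the signed-rank and Sign tests are paired procedures, and if they were run on T0 against T2 within an arm, an admission effect would become bias in that result and not just noise.

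This is a cheap improvement to the analysis, not an error that undermines the trial.

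**What to change.** - Take the admission date from the hospital record and derive the number of the 14 T0 recall days spent in the unit (0 to 14). It depends only on the admission and V0 dates, so allocation cannot affect it.
- Compare T2 CEQ-F between arms by ANCOVA, adjusted for T0 CEQ-F and that number, in place of the unadjusted t-test on change.
- Base conclusions on the between-arm contrast only, and say that within-arm CEQ-F decreases, including any from a paired fallback test, are descriptive.

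The cost is one date per patient, one or two degrees of freedom and a sentence of interpretation, with no extra visit or patient. In every case tabulated, the adjusted analysis has more power than the planned one. The T0 term brings most of the gain. The in-unit-days term helps materially only if the admission effect is about 1 SD or more: at 2 SD it adds about 2 power points (correlation 0.5) or 7 (correlation 0.7).
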